#### 2.1.6. Interventions.

The participants will be instructed not to use any cream with an active element for 2 months. All of them will receive a bottle of neutral hydrating cream for daily use in the morning and before bed. The cream formulation is composed of carbomer, cetearyl alcohol, glyceryl stearate/polyethylene glycol-100 stearate, helianthus annuus seed oil, butylated hydroxytoluene, disodium ethylenediaminetetraacetic acid, glycerin, propylene glycol, aminomethyl propanol, phenoxyethanol, ethylparaben, butylparaben, propylparaben, isobutylparaben, and aqua.

Each participant will have their face cleaned with a neutral nonalcoholic wet wipe and their eyes blindfolded and protected with goggles that allow the rest of the face to be illuminated with the red LED or with simulated light without the participant knowing which treatment was applied. A transparent plastic film will be used to cover the face before placing the LED mask, material supplied by the same manufacturer of the mask.

The equipment used will be LED masks (Cicatrillux Bio next from Cosmedical, Mauá, São Paulo—SP, Brazil) (Fig. 2), containing 92 LEDs with red wavelength (660 ± 10 nm) in the parameters described in Table 1. The application time will be 21 minutes per session, totaling 3 cycles of 7 sequential minutes due to the device’s shutdown time. The LED mask will be applied 3 times a week for 4 weeks in patients in group 1 and twice a week for 4 weeks in patients in group 2. In participants in group 3, the mask will be kept off and a white light next to the stretcher will be turned on for the participants to have the sensation of luminosity. The same beep will be emitted each cycle and the participants received the simulated application twice a week for 4 weeks.

**Table 1 T1:** LED device dosimetric parameters. Pg 10.

Parameters	Red LED
Wavelength (nm)	660 (±10 nm)
Spectral bandwidth (nm)	20
Operation mode	Continuous
The radiant power of each LED (mW)	5.02
Polarization	Random
Opening diameter of each LED (mm)	10
Irradiance at the opening of each LED (mW/cm^2^)	6.4
Beam area on target (cm^2^)	0.785
Application time (min)	21
Radiant LED exposure (J/cm^2^)	8.02
Radiant energy by LED (J)	6.3
Light emission angle	90º
Application mode	Contact
Anatomical location of application points	Face

LED = light emitting diode.

**Figure 2. F2:**
[figure not shown]
LED facial mask, Cicatrillux Bionext (Cosmedical, Mauá, São Paulo—Brazil). Pg 9. LED = light emitting diode.

### 2.2. Variables of the study

The outcomes of the study will be the evaluation of wrinkles by independent observers; analysis of the width and depth of wrinkles; wrinkle length by Image J software (National Institutes of Health, Bethesda, Maryland, https://imagej.nih.gov/ij/download.html); and assessment of satisfaction with facial appearance by participants.

#### 2.2.1. WAS.

The evaluation of wrinkles will be carried out in a standardized way using the WAS.^[29]^ This scale was developed and validated to quantify facial wrinkles based on predefined photographic models. To take photographs of the face, the participants will sign the image authorization term for use in the research and must be without any type of makeup. In a specific and reserved room, digitalized photographs of the face will be taken in the positions: front and 45 degrees right and left; with a Canon digital camera model SX510 HS 12.1 MP (Canon Do Brasil Indústria E Comércio | Ltda. São Paulo, SP, Brazil), using white LED lighting, turquoise blue background, 50 cm face distance, manual macro mode, a standard that will be followed in the photographs 30 days after the end of the treatment. The images obtained will be edited and standardized to be evaluated by the specialists according to the WAS.^[29]^ All images will be stored on a virtual disk which only the researcher will have access using a password. The images will be distributed later to the 3 plastic surgeons who will classify them according to the scale of wrinkles and photographic models pre-defined. Each evaluator will receive the same image of wrinkles, all at the end of the experiment. Each image should receive a score from 0 to 5 using the WAS as described previously.^[29,31]^ The data obtained will be grouped and the evolutionary comparison will be made according to the group of the patient under study.

To ensure homogeneity in the evaluation, an intra and interobserver agreement calculation will be performed before the sample is evaluated. Each specialist will receive 20 photographs of patients who did not participate in the study to classify facial wrinkles at any given time. After 7 days they will receive the same photographs and will need to classify the wrinkles again. The agreement index will be calculated for each evaluator and between the evaluators and an acceptable value of agreement must be above 70%.

#### 2.2.2. Analysis of the width and depth of wrinkles by optical coherence tomography (OCT).

Before treatment and after 1 month, molds of the frontal lines will be made with light condensation silicone (Clonage, DFL Indústria e Comércio, RJ, Brazil). The silicone mold obtained will be poured into special plaster in a short time. Plaster models will be sent for OCT analysis and wrinkle width and depth measured before treatment and after 1 month. The models will be made of a special type of plaster, which has greater resistance and fidelity in the reproduction of details when compared to other types (Fig. 3). Two impressions were taken for each patient, an initial one, before the application of PBM, and a final one, after the treatment was completed. The region selected for the study will be the frontal area, above the glabella. Patients will be instructed to remain in the lying position so that the impression is performed (Fig. 4).

**Figure 3. F3:**
[figure not shown]
Face impression with condensation silicone. Pg 11.

**Figure 4. F4:**
[figure not shown]
Silicone and plaster casts for optical coherence tomography analysis. Pg 11.

The OCT-CALLISTO tomograph from the Multiuser Center of the Federal University of ABC will be used to obtain the images by OCT. The plaster models obtained before and after the treatment will be evaluated with the technique. First, a visual assessment of the molds will be performed to select a visible wrinkle. The wrinkle position for analysis will be flagged to ensure that the same wrinkle and region will be analyzed before and after treatment. From the selected point, an image will be obtained with the OCT technique (Fig. 5). The images will be analyzed using a computational routine in Python language. Ten equidistant measurements of the width and depth of the wrinkle will be performed and the value obtained for calculation purposes will be the average of these measurements.

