#### 2.1.5. Blinding procedures.

The study will be carried out by a research team that will include a researcher who will carry out the application, undergraduate students, and 3 plastic surgeons who will carry out the initial evaluation of the photographs and the reevaluations after the application of the treatment (blind as to the composition of the groups), and a statistician for data processing.

The researcher responsible for the PBM application will pick and open the envelope containing the information of the experimental group in which the participant will be inserted and will proceed with the experiment. A single researcher will carry out the treatment and it will not carry out any type of evaluation. Pre and post-treatment assessments will be made by 3 examiners (3 plastic surgeons) who will not be aware of the group to which each patient will be allocated. Participants will not be aware of whether or not they have received the application of the PBM, as they will be using dark goggles. The person responsible for the application will position the equipment in the irradiation locations in all participants and will only activate the light when provided for in the specific experimental group. In the control group, the mask will be installed and kept off and a white light will be turned on close to the participant’s face so that they have a sensation of luminosity even using the blindfold. The characteristic sound of the device will be triggered by recording in the placebo group for the PBM.

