Self-assessment has become an important tool to evaluate the results of aesthetic procedures,^[38]^ facial changes resulting from aging can impact the quality of life, self-esteem, social relationships, and activities of individuals. Thus, preventive and corrective interventions are closely related not only to health but also to psychosocial well-being.^[8,9]^ In this sense, the FACE-Q questionnaire, validated for the Portuguese language, will be used to verify the level of satisfaction after treatment.

It is known that most studies that evaluate the face are based on subjective measures (patient satisfaction and photos) or using skin biopsy.^[20]^ The evaluation methods used in this research, are noninvasive, and double-blind and aim to evaluate a set of variables that can be affected or improved by PBM as a result of the frequency of application in the groups. Face photographs will be evaluated by 3 plastic surgeons using the wrinkle scale.^[29]^ These experts will be calibrated for this assessment and must achieve a rate of agreement among peers above 70%. The evaluation of the images by the Image J software, performed by a researcher not involved in this study, aims to bring quantitative data for visual analysis. The researcher will quantify in pixels the wrinkles of interest before and after treatment. The evaluation of wrinkles in plaster casts by OCT is a reliable and accurate method and there are few data in the literature that provide this type of evaluation. Therefore, in addition to contributing as an evaluation in this protocol, it could become a measurement tool in the area of aesthetics.

In summary, this clinical trial aims to contribute to clarifying the role of PBM application frequency in improving the appearance of the facial skin of menopausal women using qualitative and quantitative methodologies.

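### The OCT wrinkle is chosen by eye from the casts, with no limit to the baseline cast, no written rule and no OCT-specific masking, so the choice can depend on the outcome

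*Protocol article*

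**What the plan says.** Section 2.2.2 takes one impression before treatment and one after it, and fixes the anatomical region: "The region selected for the study will be the frontal area, above the glabella". The paragraph after Figure 4 then gives the OCT procedure in this order:

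- It opens by naming the casts from both visits as the objects to be examined.
- The line is then chosen as follows: "First, a visual assessment of the molds will be performed to select a visible wrinkle".
- To keep the two visits comparable, the plan adds a marking step: "The wrinkle position for analysis will be flagged to ensure that the same wrinkle and region will be analyzed before and after treatment".
- Only after that does a Python program read the OCT images. Along the chosen line, ten evenly spaced readings of each dimension are taken, and their mean is analysed.

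On masking, section 2.1.5 says: "Pre and post-treatment assessments will be made by 3 examiners (3 plastic surgeons) who will not be aware of the group". The same section describes these surgeons as rating photographs, and it bars the researcher who applies the treatment from any evaluation. Section 2.2.3 states that the Image J reader is blind to group. Section 2.2.2 has no corresponding sentence. The Discussion makes a general statement: "The evaluation methods used in this research, are noninvasive, and double-blind".

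**The concern.** The plan fixes the forehead region but not the line within it. A forehead may carry several lines, and the only stated criterion is that the chosen one be visible. If the final cast can be seen when the choice is made, the measured site may depend on the result being measured. Two mechanisms pull in opposite directions:

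- **Persistence.** A line that has flattened by follow-up is less visible and may be passed over for one that remains. This hides response.
- **Improvement.** A selector with both casts in hand may settle on the line that changed most. This exaggerates response.

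The Discussion criticises subjective instruments and presents OCT on casts as a reliable and accurate method. A subjective choice of site made with the outcome in view would undercut that claim.

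**Working it through.** The documents give no effect size, SD or sample size for OCT, so there is no stated figure to reproduce. The check is a reading of the text followed by an illustration whose inputs are assumptions.

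**1. What each safeguard covers.**

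| Provision | What it prevents | Does it stop the final cast influencing the choice? |
|---|---|---|
| Fixed frontal region (2.2.2) | choice of a different area of the face | No; the line within the region is open |
| Flagged position (2.2.2) | measuring different lines at the two visits | No; it acts once a line is chosen |
| Python routine and ten averaged readings (2.2.2) | reading error and discretion along the line | No; both act within the chosen line |
| Treating researcher excluded from evaluation (2.1.5) | evaluation by the person who opens the envelope | No; it concerns the arm, not the visit |
| General double-blind statement (Discussion) | knowledge of the arm, if applied to OCT | No; it does not say that visit is hidden |

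**2. Within-arm shift if the most improved line is picked, with no true effect.** Assume k equally visible lines with independent changes of SD s. The expected change of the selected line is E_k × s, where E_k is the expected maximum of k independent standard normals, E_k = ∫ x k φ(x) Φ(x)^(k−1) dx.

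- k = 2: 0.56 s
- k = 3: 0.85 s
- k = 4: 1.03 s

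This is a worst case. It assumes that the eye always finds the most improved line and that lines on one forehead change independently.

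**3. The same shift in units of depth.** Let observed depth on one cast have SD 1 across lines, with test-retest reliability r. Change due to error alone then has s = √(2(1−r)), which is 0.447 at r = 0.9 and 0.775 at r = 0.7. E_5 is 1.163.

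- Most improved line, 3 lines, r = 0.9: 0.846 × 0.447 = 0.38
- Most improved line, 5 lines, r = 0.7: 1.163 × 0.775 = 0.90
- Deepest baseline line, 3 lines, r = 0.9: 0.846 × 0.1 = 0.09 (regression to the mean)
- Deepest baseline line, 5 lines, r = 0.7: 1.163 × 0.3 = 0.35 (regression to the mean)
- Line chosen without regard to change: about 0

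**4. Between-arm difference with no true effect.** If the selector is group-blind, each arm shifts by E_k s, and the difference is E_k s − E_k s = 0. If the selector knows the arm and favours improvement only in the active arms, the whole of E_k s can enter the comparison.

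**5. Between-arm difference with a real effect and a group-blind selector.** Assume baseline depth SD 1, a true arm difference of 0.5, a control change SD of 0.5, 2 to 4 lines and no measurement error.

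- **Most improved line.** The estimate is 0.5 + E_k (s_active − s_control). With equal SDs it is 0.50. With an active SD of 0.75 it is 0.5 + 0.25 × 0.56 = 0.64 for 2 lines and 0.5 + 0.25 × 1.03 = 0.76 for 4.
- **Line most visible on both casts** (largest value of the smaller of its two depths, by simulation). With equal SDs the estimate falls to 0.46 for 2 lines and 0.42 for 4. With an active SD of 0.75 it falls to about 0.36 and 0.27.
- **Deepest line on the baseline cast.** The estimate is 0.50 throughout.

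Group masking alone therefore does not make the rule safe when treatment works. Selection on the baseline cast does, under these assumptions.

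**The case against.** The strongest reply is that the text does not say when the wrinkle is chosen. The plural for the casts may simply range over participants, and flagging at baseline with later re-location fits the words. A reader might infer that the plan has the choice made after both casts exist. That is the natural reading of the sentence order, but the article does not state it. What stands is that nothing in the wording prevents it.

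A reader might also infer that OCT is unmasked. The documents do not support that either. The Discussion calls the evaluation methods double-blind in general, and section 2.1.5 keeps the treating researcher out of all evaluation. A condensed article may also leave the coding of casts to the full protocol. The accurate statement is narrower: section 2.2.2 names no masked OCT selector or measurer and does not hide the visit.

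It is also fair to say that this is a three-arm comparison with a sham, so a shift common to all arms is not a treatment effect. That holds with no effect and group-blind selection. It need not hold when there is a real effect, as step 5 of the working shows.

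Finally, the two mechanisms oppose each other, so no net direction is shown. This is correct, and none is claimed.

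**Conclusion.** The concern holds in this limited form. The stated rule lets one wrinkle be chosen by eye with the final cast in view, and none of the stated safeguards closes that gap. Within-arm width and depth change can be biased in either direction. The between-arm comparison is at risk if the selector knows or guesses the arm, or if selection interacts with a real effect. With no effect and group-blind selection the bias largely cancels.

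The size cannot be derived from the documents. The 0.56 to 1.03 SD figure is a worst-case within-arm shift that assumes 2 to 4 independent lines and perfect picking of the most improved. It is tempting to set it beside the planned effect on the Wrinkle Assessment Scale (WAS), but that is a between-arm difference on another outcome and the comparison is not valid. The sample size rests on WAS, so the point affects OCT width and depth and not the outcome that sized the trial. The change is still worth making because it is cheap and supports the precision the article claims for OCT.

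**What to change.** In section 2.2.2, state that:

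1. The wrinkle is selected and flagged on the baseline cast only, before the final cast is viewed.
2. Selection follows a written rule, for example the line at a fixed position above the glabella, or the deepest line on the baseline cast. The second option brings regression to the mean, which is expected to be equal across randomised arms.
3. The same flagged site is measured on the final cast even if the wrinkle has flattened, and near-zero depths are kept in the analysis.
4. Casts carry codes, so that the person who selects and the person who measures do not know the arm.

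The cost is wording plus coding of casts that are already being made. There is a small practical burden: the site has to be re-located on a second, separate impression, so the text should say by what landmark this is done.

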**Figure 5. F5:**
[figure not shown]
Image of the wrinkle impression obtained by OCT. Pg 12. OCT = optical coherence tomography.

#### 2.2.3. Quantitative evaluation of wrinkles.

The same images obtained for expert evaluation will be analyzed by the Image J software to quantify wrinkles. They will be quantified by the variation of pixels in the image of frontal wrinkles, periorbital, glabella, and nasolabial folds before and after 1 month of treatment. The ImageJ software analyzes the image by the intensity or gray level of the pixels. The calculation of the areas is done by counting the pixels of the selected regions.^[32]^ A researcher who was not involved in the study will take the measurements and will not know which treatment group the patient belongs to. Therefore, the evaluator will be blind regarding the group but will need to know which image was the before and after to compare the measurements of the same wrinkles.

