## Abstract

**Methods and analysis::**

The objective of this study is to compare the effects of PBM with a light-emitting diode mask (660 nm, 6.4 mW/ cm², 8,02 J/ cm², 5.02 mW, 21 minutes) on facial rejuvenation using 2 frequency applications for 4 weeks: one group will receive PBM application on the face, twice a week and another group will receive PBM application 3 times a week. A group with simulated PBM applied twice a week for 4 weeks will be used as a control. The treatment will be performed on female participants aged between 45 and 60 years. After 4 weeks, evaluations of photographic images by specialists (Wrinkle Assessment Scale) as well as the quantitative analysis of the wrinkle size by the Image J software, the depth and width of wrinkles (assessment of face impressions by optical coherence tomography) and the level of Satisfaction with Facial Appearance Overall will be compared with data collected before the start of the study. All data will be analyzed statistically according to their distribution, seeking a level of statistical significance of 0.05.

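### The Image J reader is told which image is before and which is after, although matching wrinkles needs only the pairing; this can inflate change from baseline in every arm, but not the between-arm comparison while group masking holds

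*Protocol article*

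**What the plan says.** **Image J (section 2.2.3).** A researcher from outside the study measures frontal, periorbital, glabellar and nasolabial wrinkles on the photographs taken before treatment and one month later. Areas come from counting pixels in selected regions. This researcher "will not know which treatment group the patient belongs to". On time point the section goes the other way: "the evaluator will be blind regarding the group but will need to know which image was the before and after", and the purpose given is "to compare the measurements of the same wrinkles".

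**Wrinkle Assessment Scale, WAS (sections 2.1.5 and 2.2.1).** This is the outcome on which section 2.1.3 bases the sample size. Section 2.1.5 lists, as part of the team, "3 plastic surgeons who will carry out the initial evaluation of the photographs and the reevaluations after the application of the treatment", and describes the examiners as people "who will not be aware of the group to which each patient will be allocated". Section 2.2.1 says "The images will be distributed later to the 3 plastic surgeons" and then "Each evaluator will receive the same image of wrinkles, all at the end of the experiment".

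**Use of the results.** The abstract says the post-treatment evaluations "will be compared with data collected before the start of the study". Section 2.3 plans repeated-measures ANOVA, with Tukey comparisons if the groups differ.

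**The concern.** Finding the same wrinkle in two photographs requires knowing that they come from one participant. It does not require knowing which was taken first. The protocol therefore gives up masking to time point for a reason that does not call for it.

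Section 2.2.3 has a researcher take the measurements on selected regions, which I read as regions chosen by hand. A reader who expects wrinkles to shrink can draw the later region slightly smaller without knowing the arm. The result is an apparent improvement in all three arms, sham included. It would appear in the before-after change and in the time effect of the repeated-measures ANOVA. The abstract's comparison with baseline makes that a reading the eventual report may well offer. The Discussion also presents Image J as the quantitative complement to visual rating, so an avoidable expectation effect is unwelcome here.

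The WAS raises a smaller, separate question. The two sections that describe the surgeons' rating can be read as different schedules, and under one of them the surgeons would know the visit.

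**Working it through.** **1. Does the stated reason require the order?** Section 2.2.3 wants the same wrinkles compared. Section 2.2.2 faces the same task with the plaster casts and solves it by flagging the wrinkle position, so that one site is measured both times. The protocol thus already contains a way of matching that does not depend on the reader knowing the order.

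**2. Where does a reader shift go?** Let δ be the true mean reduction in an arm and b an amount that expectation adds to the reduction, the same in every arm because the reader does not know the arm.

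- Reported reduction within an arm: δ + b, so it is too large by b.
- Reported difference between arms: (δ_active + b) − (δ_sham + b) = δ_active − δ_sham, so b cancels.

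**3. How large could the within-arm effect be?** The protocol gives no standard deviation for Image J and no figure for reader expectation. The illustration below therefore depends only on the ratio of the shift to the SD of the change.

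Inputs:
- 24 participants per arm and three arms (section 2.1.3).
- SD of change, taken from the two WAS change SDs quoted in section 2.1.3: √[(0.7² + 0.5²)/2] = √0.37 = 0.608. It serves only to scale the shift.
- Common shifts of 0, 0.1, 0.2 and 0.34. These are assumptions. Divided by 0.608 they are 0, 0.16, 0.33 and 0.56 SD.
- No true change in any arm, normally distributed changes, 20,000 simulated trials per setting, two-sided 5% tests.

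| Common shift (SD of change) | Time effect significant | One arm's before-after test significant | Group-by-time significant |
|---|---|---|---|
| 0 | 5% | 5% | 5% |
| 0.16 | 29% | 12% | 5% |
| 0.33 | 79% | 34% | 5% |
| 0.56 | 99.7% | 75% | 5% |

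As a check on the third row, the expected test statistic for the time effect is 0.2 × √72 / 0.608 = 2.79, against a critical value of about 2.0. For a single arm it is 0.2 × √24 / 0.608 = 1.61, against about 2.07. Both agree with the simulated rates.

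**4. What if group masking failed?** If only the two active arms were shifted, by 0.16, 0.33 or 0.56 SD, the between-group test would reject in about 8%, 20% or 49% of trials with no true effect. Nothing in the protocol says that it fails.

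**5. The WAS wording side by side.** Section 2.1.5 speaks of an initial evaluation and of re-evaluations after treatment. This can describe rating sessions held at different times, or simply the scoring of baseline and post-treatment photographs. Section 2.2.1, which sets out the procedure, has the images stored, sent out later and received at the end. The second reading of 2.1.5 agrees with 2.2.1; the first does not.

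**The case against.** The strongest reply is that the trial's question is comparative. Section 2.1.3 sizes the study for a difference between groups, section 2.3 makes the Tukey comparisons depend on one, and the readers are masked to group. A shift common to all arms cancels, and the sham arm is there to absorb it. This stands. A reader might infer from the unmasked order that the treatment comparison is biased, but the documents do not support that. Step 2 shows the cancellation, and the last column of the table stays at 5%.

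A second reply is that section 2.1.5 only lists staff, while 2.2.1 gives the operative procedure. This largely stands too. A reader might infer that the surgeons will know the visit and that rater drift will enter the WAS change. That follows from only one reading of a loose sentence, and 2.2.1 points the other way. A floor effect on the 0 to 5 scale might also be inferred, but no baseline WAS values are given and nothing supports it.

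A third reply is that coding and shuffling the WAS images is detail that an article may leave to the full protocol. That is fair, so its absence is not held against the plan. The Image J sentence is different: it is an explicit choice to unmask, not an omission.

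None of these replies supplies a reason for the Image J reader to know the order.

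**Conclusion.** The point holds within limits. For Image J the unmasking of order is stated outright, is unnecessary for its stated purpose, and can inflate the before-after change and the time effect in every arm. The between-arm comparison is not biased as long as group masking holds and expectation acts alike in all arms.

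The size cannot be derived from the documents. Over assumed shifts of 0.16 to 0.56 SD of the change, with 24 per arm and no true change, a false time effect would appear in about 29% to 99.7% of trials and a false within-arm improvement in about 12% to 75%. The illustration assumes normal changes and borrows its SD from WAS figures, so it shows the mechanism and is not an estimate for Image J areas.

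For the WAS the finding is an inconsistency of wording between sections 2.1.5 and 2.2.1. It is not an established loss of masking.

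**What to change.** **Section 2.2.3.** Replace the statement that the reader must know the order. Give the reader each participant's two images as a pair labelled A and B in random order, with dates removed from file names and metadata. Mark the location of the wrinkle regions in advance on both images, as section 2.2.2 does for the casts. The marks should show location only, so that expectation does not move into the marking step. Reveal the order only after all measurements are recorded.

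**Sections 2.1.5 and 2.2.1.** Reword 2.1.5 to agree with 2.2.1: all baseline and post-treatment photographs are rated by the three surgeons at the end of the experiment. In that single session, present the images in random order without visit labels.

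**Cost.** A few hours of file coding, and a key held by someone who does not measure or rate. Visits, participants and sample size do not change, and section 2.2.1 already plans the WAS rating for the end.
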